## Abstract

**Objective::**

To evaluate the effectiveness of nudge activities at school on the students’ body mass index (BMI).

**Design::**

School-based factorial randomized community trial.

**Setting::**

Eighteen public schools in the municipality of Duque de Caxias, metropolitan area of Rio de Janeiro, Brazil.

**Participants and intervention::**

The 18 schools will be randomized into 4 group arms: group 1—control (without any activity); group 2—will receive educational activities in the classroom; group 3—will receive changes in the school environment (nudge strategies); group 4—will receive educational activities and changes in the school environment. Activities will occur during the 2018 school-year.

**Main outcome measure(s)::**

The primary (BMI) and secondary (body fat percentage) outcomes will be assessed at baseline and after the study using a portable electronic scale with a segmental body composition monitor. The height will be measured by a portable stadiometer.

**Analysis::**

Statistical analyses for each outcome will be conducted through linear mixed models that took into account the missing data and cluster effect of the schools.

## Introduction

1

In Brazil, 1 in 5 adolescents are overweight or obese.^[1]^ Environmental factors have great influence on the genesis of the obesity epidemic, due mainly to the consumption of energy-dense foods, low levels of physical activity, and sedentary lifestyle. Thus, these 2 components—diet and energy expenditure—are the cornerstones of prevention and treatment programs of obesity.^[2,3]^

Interventions in schools to prevent obesity have been established as an important strategy to address the problem, but previous research has shown that interventions towards healthy behaviors have had humble results.^[4]^ Observed effects imply high levels of knowledge, awareness, and positive attitude towards healthy eating,^[5]^ yet underscoring the problem that information and positive attitudes are not enough to produce actual change.

In this context, some interventions have used nudge strategy to alter people's behavior in a predictable way to make healthy behavior more likely.^[6,7]^ Nudging is an aspect of the choice architecture (the way of presentation and framing of choices) that alters the individuals’ choice in a predictable and desirable way, without forbidding any options or significantly changing their economic incentives,^[8,9]^ assuming that individual behavior is strongly influenced by the environment in which decisions are taken.^[10]^

Some studies conducted in developed countries have reported success in nudge interventions. Williamson et al^[11]^ observed positive results in food consumption after several changes in the school cafeteria environment. Wansink et al^[12]^ found a positive effect in making vegetables more attractive, by giving them nicknames, increasing their consumption in American school cafeterias. However, some studies did not find significant association between the use of nudge and healthier eating by the adolescents investigated. Bucher et al^[13]^ observed that point-of-purchase messages had no effect on vegetable basket sales in a college foodservice setting. Coyle et al^[14]^ showed that the presence of a salad bar was not associated with greater fruit and vegetable consumption in elementary schools.

Systematic reviews showed that the choice architecture seems effective to promote healthier food choices,^[13,15]^ and the most effective strategy was to increase food availability.^[16]^ However, the authors concluded that there is an important literature gap,^[7]^ and few high-quality studies evaluated nudge strategy in real-life scenarios^[13,15]^ and quantified the impact of these strategies on health outcomes, mainly obesity.^[13,17,18]^

Adolescents are highly susceptible to environmental influences, suggesting that nudging is an interesting tool in the prevention of obesity and school a strategy place to promote nudging.^[7]^

This project is a factorial trial which continues previous research called PAAPPAS study (Portuguese abbreviation of “parents, students, community health agents and teachers for healthy eating”).^[19]^ The present project will be conducted in schoolchildren, keeping the already consolidated components of primary prevention and including actions that aim to improve the adherence response to the interventions and providing a broad spectrum of actions to reach adolescence-based obesity prevention, including changes in School environment. More specifically, the present research aims to estimate the effect of “nudge” strategies on the students’ body mass index (BMI), from changes at the school environment, with the aim of creating school cafeterias that guide smarter food choices.

## Methods

2

### Sample size calculation

2.2

Sample size of PAAPPAS Nudge was calculated based on a minimum effect of 0.15 in BMI variation and considering intra and intergroup comparisons. A sample size of 640 adolescents was required based on 95% power and a correlation between repeated measures of 0.5. Considering the intracluster correlation and refusal rate, the total sample size required was increased, leading 1300 adolescents, which can be achieved achieved with 10 schools with 4 to 5 classes of 30 students each one.

In addition, a subsample of 96 adolescents (48 boys and 48 girls) was calculated to detect a mean difference in daily energy expenditure of 110 kcal and a coefficient of variation equal to 1 (standard deviation [SD] of 110 kcal),^[23]^ with an α of 0.05 (2-sided) and β of 0.10.^[24]^ The adolescents were sampled from 1 intervention (n = 48) and 1 control school (n = 48).

### Intervention

2.3

The activities will occur during the 2018 school-year and will combine different intervention strategies: educational interventions (in the classroom) and modifications in the environment (school canteens and sports court).

Group 2 will receive classroom-based educational activities based on an earlier study, which was developed in the same city and constituted a school-based intervention with the objective of reducing the consumption of sweetened beverages and biscuits, and increase the consumption of fruits, vegetables, and beans.^[25]^

In group 3, changes in the environment will be included that will facilitate both physical activity and healthy food choices. Interventions will be based on a nudge strategy, a tool of the architectural field of choice, which is defined as a way of influencing choices without limiting personal decisions or having to implement actions or interventions of greater cost and operational difficulty.^[26]^ The concept of nudging is based on the theory of the double process originated in the field of psychology, which involves the division of human cognition into 2 systems: the reflective and the automatic. The first is rational and involves conscious decisions, whereas the latter is more controlled by instinct.^[27,28]^ These 2 systems are taken into account for a number of cognitive biases, which explains, for example, why people, though conscious, have difficulty in translating intentions into actions. Using the understanding of these 2 biases is possible to changing behavior developing new ways of how food choices are presented in an environment, and individuals are unconsciously “motivated” to adopt healthy choices.

The approaches can be divided into passive and active. The passive approach, also called choice architecture, seeks to induce healthy choices through small changes in the environment. The active approach includes placing reminders in the environment. In the school context, the intention is to change the environment in which schoolchildren are inserted with the perspective of associating convenience with healthier practices and making less healthy practices less convenient, aiming to increase the consumption of healthier foods and stimulate the practice of physical activity. The convenience of healthy practices both preserves the power of choice (students are not required to consume healthy food or engage in physical activity) and encourages healthy behavior.^[17]^

Table 1 describes the intervention components and evaluation tools conducted in PAAPPAS Nudge.

**Table 1 T1:**
[figure not shown]
Intervention components, description, and evaluation.

Interventions regarding food consumption were based on those strategies of the Smarter Lunchrooms Movement (SLM)—an intervention study conducted in US school lunchrooms to led students to eat more fruits and vegetables, with positive results.^[29]^ In the present study, school lunchrooms will be the central place of modifications regarding food consumption, where the strategies that were effective in SLM will be reproduced:1)Arrange the fruits served in the school lunch in a prominent position, in containers of bright and contrasting colors, to serve them. In this approach the student himself is served, which will probably result in his ingestion.2)Creative names for food served at meals will be created by the students used on displays at canteen tables, posters on the way of the cafeteria, and at a menu outside the cafeteria. Increasing students’ expectancy increases their likelihood of choosing and eating new dishes. Students will be encouraged to participate actively in this stage. They will receive a list of the most commonly served vegetables at the lunch and will be asked to create fun-filled names for each of them, such as “carrots x-ray vision” and “super strength spinach.”

Moreover, to encourage water consumption, footprints that lead them to water fountains will be painted on the floor. To stimulate physical activity, several sports equipment (basketball hoops, volleyball nets, balls, ropes, shuttlecock, and a lot of toys) will be available for use in the school sports court. The courts will be renovated and footsteps will be painted to nudging students to the sports equipment.

Group 4 received both interventions.

The measurable intervention outcomes are fruits, vegetables, and water consumption (quantities in g or mL) obtained from the 24-hour recall, and estimated physical activity and daily energy expenditure.

### Data collection

2.4

#### Physical activity

2.4.1

Physical activity levels will be measured through a validated questionnaire including 6 questions about frequency and time of different physical activities domains (commuting to school, physical education classes, and other physical activities/sports) performed during the previous 7 days. Adolescents will be classified as active (≥300 minutes), insufficiently active (150–299 and 1–149 minutes), and inactive (no physical activity) according to their accumulated physical activity level.^[30]^ In addition, total energy expenditure will be measured using triaxial accelerometers (Actigraph, GT3X)^[31]^ in a subsample of 96 adolescents (48 boys and 48 girls). The accelerometers will be placed on the right hip (anterior iliac crest) during a 6-day period, except while bathing or during water activities.

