### Statistical analysis

2.6

Statistical analyses for each outcome are conducted through linear mixed models that took into account the missing data and cluster effect of the schools. The models will be used to assess the impact of treatment (nudge or control school), time (treated as continuous, in months), and the treatment-by-time interaction. In this analysis, the distribution of probabilities more suitable for the variable of interest will be verified, and also the correlation structure between repeated measurements. Data analysis will be performed using the Statistical Analysis System, version 9.4 (SAS Institute Inc, Cary, NC).

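### The accelerometer outcome is absolute total kcal per day, which depends on body weight as well as activity, and neither the outcome nor the stated model allows for weight

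*Protocol article*

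**What the plan says.** Section 2.4.1 measures physical activity in two ways. All pupils answer a questionnaire that is scored in minutes. In a subsample of 96, "total energy expenditure will be measured using triaxial accelerometers" worn on the hip for six days.

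Section 2.2 sizes the subsample "to detect a mean difference in daily energy expenditure of 110 kcal", with a "coefficient of variation equal to 1 (standard deviation [SD] of 110 kcal"), "with an α of 0.05 (2-sided) and β of 0.10". The pupils come from one intervention school (48) and one control school (48).

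The end of section 2.3 lists "estimated physical activity and daily energy expenditure" among the measurable outcomes of the intervention.

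Section 2.6 gives one type of model for each outcome: "The models will be used to assess the impact of treatment (nudge or control school), time (treated as continuous, in months"), and the interaction of the two. No weight term is named. Section 2.5.1 has body weight measured by scale.

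**The concern.** The subsample gives the trial its only device-based evidence on whether the renovated courts and sports equipment raise activity. The outcome chosen is total expenditure in absolute kcal. It is not expressed per kg, not restricted to expenditure on activity, and not a count of movement. Total kcal per day rises with body mass at the same level of movement. Two things follow.

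- **Interpretation.** If the pupils in one school are heavier, that school can appear more active without moving more.
- **Precision.** Variation in body size sits in the error term of the comparison, although the variable that would remove it is already collected.

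The Discussion presents the effect of environmental change on physical activity as an innovative part of the trial, so the measure should be one that can be read as activity.

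**Working it through.** **Inputs from the documents.** Target 110 kcal per day, SD 110 kcal, two-sided alpha 0.05, power 0.90, 48 v 48 pupils (section 2.2). Planned BMI effect 0.15 (section 2.2; unit not stated, read here as kg/m²).

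**Assumed inputs (not in the documents).** Slope of 20 to 45 kcal per day per kg, weight SD of 8 to 12 kg, height of 1.40 to 1.50 m. A wider range is used in step 5.

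**1. The plan's own figure.** n per group = 2 × (1.960 + 1.282)² × (110/110)² = 21.0, so 22 (23 by the t-test). Done separately for boys and girls, the total is 4 × 22 = 88, or 4 × 23 = 92. The stated 96 is 24 in each of four sex-by-school cells, slightly more than needed. With 48 v 48, power on the stated inputs is 99.8%. The subsample is not too small on its own terms.

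**2. Weight difference equivalent to the target.** 110/45 = 2.4 kg and 110/20 = 5.5 kg. With a lower slope of 10 kcal per kg it would be 11 kg, so the concern shrinks as the slope falls.

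**3. Dilution from success on BMI.** A fall of 0.15 kg/m² is 0.15 × 1.40² = 0.29 kg to 0.15 × 1.50² = 0.34 kg. Multiplied by 20 and 45, this is about 6 to 15 kcal per day, or 5% to 14% of the target.

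**4. Precision, under each reading of the SD.**

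- *If 110 kcal is the total spread*, weight is already inside it. Suppose weight explains 25%, 50% or 75% of the variance. Adjustment then cuts the required n per group from 22 to 16, 11 or 6, from 21.0 × (1 − R²). The chance difference due to weight between two groups of 48 is at most 110 × √(2/48) = 22 kcal (1 SE).
- *If 110 kcal is the spread left after weight*, the weight-driven SD is 20 × 8 = 160 to 45 × 12 = 540 kcal. The total SD is √(110² + 160²) = 194 to √(110² + 540²) = 551 kcal. Power with 48 v 48 falls to between 78% and 16%. The chance difference (1 SE) is 33 to 110 kcal.

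The document does not say which reading applies.

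**5. Share of the spread due to body size.** With 5 to 30 kcal per kg and a weight SD of 5 to 12 kg, the weight-driven SD is 25 to 360 kcal. If the remaining SD is 110 kcal, the share of variance is 25²/(25² + 110²) = 5% to 360²/(360² + 110²) = 91%. At 10 kcal per kg and 10 kg it is 45%; at 15 kcal per kg and 8 kg it is 54%.

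**The case against.** **The model may remove weight by itself.** The effect in section 2.6 is the treatment-by-time term. If the device is worn at baseline and again later, stable weight differences largely cancel. This stands as a condition, but section 2.4.1 states only a six-day period and does not say how often it is repeated. Section 2.2 sizes a plain difference in means, without the correlation between repeated measures that it uses for BMI.

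**A weight covariate may be specified elsewhere.** This is fair: the article is condensed, Table 1 is not shown, and an analysis plan may exist. The point therefore rests on what is stated, namely an absolute kcal outcome with an absolute kcal target and SD, more than on the missing covariate.

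**Total expenditure is a coherent measure in an obesity trial, and activity is also measured by questionnaire.** Both are true. The Introduction names diet and energy expenditure together, and questionnaire minutes do not scale with weight. But the questionnaire is self-report, and the device is the objective check on it. Keeping kcal as an energy-balance measure is reasonable; reading it alone as activity is not.

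**One school per arm limits any gain.** This stands. Adjustment for weight cannot separate the treatment from the school.

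**Stronger readings that a reader might infer.** One is that most of the spread is body size. The documents give neither a slope nor a weight SD, and the share runs from 5% to 91%. Another is that the outcome moves the wrong way when BMI improves. The direction is right at fixed activity, but 6 to 15 kcal against 110 dilutes a gain and does not reverse it. A third is that the subsample is underpowered, at 78% down to 16%. That requires the SD of 110 kcal to be weight-adjusted, which the document nowhere says.

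**Conclusion.** The concern holds as a point about the stated outcome. Absolute total kcal per day mixes body size with activity, and the text shown makes no allowance for this although weight is measured. Under an assumed 20 to 45 kcal per day per kg, a weight difference of 2.4 to 5.5 kg between the groups would reproduce the whole target effect with no difference in activity. The loss of precision is real but cannot be sized from the documents, because it depends on what the SD of 110 kcal describes. The bias from the planned BMI effect is minor. The point concerns neither the primary outcome nor the named secondary outcome, and it carries less weight if the device is worn repeatedly and change is analysed.

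**What to change.** - **Sections 2.4.1 and 2.6.** Adjust daily kcal for baseline body weight and sex, and give the unadjusted figure as descriptive. Beside it, report a measure from the same recordings that does not scale with weight: mean counts per minute, or minutes of moderate-to-vigorous activity per valid day. Name one of the two in advance. Adjustment for baseline weight leaves the small BMI-driven dilution in place; the movement measure avoids it.
- **Section 2.2.** State whether the SD of 110 kcal is the total or the weight-adjusted spread, as its source supports. It should not be declared weight-adjusted without that support.

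**Cost.** Wording in three sections and two covariates that are already available; no new pupils, visits or measurements. The downside is that the headline result is no longer a raw kcal difference. The change does not cure the confounding of treatment with school in this subsample, and the report should say so.

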#### Food consumption

2.4.2

Food intake will be assessed by a food frequency questionnaire validated for teenagers in Rio de Janeiro^[32]^ and one 24-hour recall (Rec24-h). Netbooks containing a computer program developed for school use^[27,33]^ based on a technique called “Multiple Pass Method”^[34]^ will be used.

### Expected outcomes

2.5

#### Primary and secondary outcomes

2.5.1

The primary outcome of the study will be the variation of BMI and secondary outcome will be the variation of body fat percentage.

The body weight and body fat percentage will be measured by a portable electronic scale with a segmental body composition monitor (Tanita BC-558). The height will be measured by a portable stadiometer (brand: “AlturaExata”). The waist circumference will be measured with an inextensible measure tape, with amplitude of 150 cm and variation of 0.1 mm. All the measures will be taken according the protocol designed by Gordon et al.^[35]^ Each adolescent will be evaluated 3 times: baseline—at the begging of the school-year, the second—at the middle of the school-year; and the third—at the end of the school-year. To avoid follow-up losses, schools will be visited three times in each measurement time.

### Statistical analysis

2.6

Statistical analyses for each outcome are conducted through linear mixed models that took into account the missing data and cluster effect of the schools. The models will be used to assess the impact of treatment (nudge or control school), time (treated as continuous, in months), and the treatment-by-time interaction. In this analysis, the distribution of probabilities more suitable for the variable of interest will be verified, and also the correlation structure between repeated measurements. Data analysis will be performed using the Statistical Analysis System, version 9.4 (SAS Institute Inc, Cary, NC).

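### The BMI model is valid but leaves each arm's baseline mean free; using the baseline value would cut variance by about 25% before school clustering, and about 6% to 23% with it

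*Protocol article*

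**What the plan says.** The section on primary and secondary outcomes (2.5.1) states: "The primary outcome of the study will be the variation of BMI". Body fat percentage is the secondary outcome. The same section sets the schedule: "Each adolescent will be evaluated 3 times", at the start, middle and end of the school-year.

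The statistical analysis section (2.6) specifies "linear mixed models that took into account the missing data and cluster effect of the schools" and then lists the effects: "The models will be used to assess the impact of treatment (nudge or control school), time (treated as continuous, in months", followed by the interaction of the two. It leaves two items to be checked on the data: the probability distribution of the outcome, "and also the correlation structure between repeated measurements". It names neither baseline adjustment nor a common baseline mean.

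The sample size section (2.2) gives the planning correlation: "A sample size of 640 adolescents was required based on 95% power and a correlation between repeated measures of 0.5". That 640 is then raised to 1300 for clustering and refusal. No ICC or refusal rate is given.

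**The concern.** A treatment main effect beside a time variable that starts at baseline lets each arm have its own mean at time zero. The treatment-by-time term then carries the whole treatment effect, and it is a difference in change that makes no use of the baseline level.

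Schools are randomised and baseline is measured at the start of the year, so the arms have the same expected baseline. Estimating separate baseline means spends information on differences that are zero in expectation. A model that adjusts for baseline, or gives all arms one baseline mean, recovers that information from measurements the trial already takes. Only precision is at stake. With 18 schools in four arms, precision is scarce enough for this to be worth a sentence in the plan.

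**Working it through.** **Inputs from the article.** Planning correlation ρ = 0.5, 640 adolescents, 95% power and 1300 after inflation (section 2.2); 18 schools and four arms (section 2.1); three waves (section 2.5.1).

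**Assumptions (not in the article).** Two-sided α of 0.05; equally spaced waves; complete data; equal arms; compound symmetry unless stated; 1300/18 ≈ 72 pupils per school; ICC 0.005 to 0.05; correlation of school effects between waves (κ) 0.8 to 1.0.

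**Step 1: the plan's 640.** A repeated-measures calculation for the group-by-time interaction has λ = f²·N·m/(1−ρ). With four groups, m = 3, ρ = 0.5 and f = 0.075 (a standardised difference of 0.15), 95% power needs N = 624. At N = 640, λ = 0.075² × 640 × 3/0.5 = 21.6 and power is 0.956. Alternatively, f = 0.15 needs N = 160, and 4 × 160 = 640. The article gives no SD, α or number of groups for this calculation, so these are plausible readings, not confirmed ones. Neither relies on baseline adjustment, so planned power does not depend on the change proposed here.

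**Step 2: what the listed terms estimate.** With waves coded 0, 1, 2, free baselines and compound symmetry, the variance of the difference in slopes, per σ²/n, is 2(1−ρ)/Σ(t−t̄)² = 2(1−ρ)/2 = 1−ρ. Over two time units that is 4(1−ρ) = 2.00 at ρ = 0.5. The first-to-last change contrast has variance 2 × 2(1−ρ) = 2.00. The two coincide.

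**Step 3: gain before clustering.**
- Two waves: change score 2(1−ρ) = 1.00; baseline-adjusted 1−ρ² = 0.75. The ratio is (1+ρ)/2 = 0.75, so variance falls 25% and the standard error 13.4% (1 − √0.75).
- Three-wave slope with a common baseline: ratio 2(1+2ρ)/(5+ρ) = 4/5.5 = 0.727, a 27% gain. Under AR(1) with a first-to-last correlation of 0.5 the ratio is 0.749.
- At ρ = 0.7, 0.8, 0.9 and 0.95 the two-wave gain is 15%, 10%, 5% and 2.5%.

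**Step 4: gain with schools as the randomised unit.** For a school mean of m = 72 pupils (total variance 1):
- variance at a wave v = ICC + (1−ICC)/m
- covariance between waves c = ICC·κ + (ρ − ICC·κ)/m
- correlation of school means q = c/v, which replaces ρ in step 3

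Low end of the ICC range (ICC 0.005, κ 0.8): v = 0.01882, c = 0.01089, q = 0.579. Three-wave ratio 2(2.158)/5.579 = 0.773, a gain of 22.7%.

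High end (ICC 0.05, κ 1.0): v = 0.06319, c = 0.05625, q = 0.890. Three-wave ratio 2(2.780)/5.890 = 0.944, a gain of 5.6%.

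Variance reduction at ρ = 0.5, three-wave slope (two-wave or year-end contrast in brackets):

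| ICC | κ = 0.8 | κ = 0.95 | κ = 1.0 |
|---|---|---|---|
| 0.005 | 22.7% (21.1%) | 20.4% (19.1%) | 19.7% (18.5%) |
| 0.01 | 20.0% (18.8%) | 16.5% (15.7%) | 15.4% (14.6%) |
| 0.05 | 13.9% (13.3%) | 7.6% (7.4%) | 5.6% (5.5%) |

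In standard-error terms the extremes are 1 − √0.944 ≈ 3% and 1 − √0.773 ≈ 12%. At ρ = 0.9 the bracketed gains fall to between 1.1% and 8.9% over the same range of ICC and κ.

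**Step 5: does the remedy carry a cost under linear time?** Suppose there is no effect at mid-year and a full effect of 1 at year-end, with no school effect. The free-baseline linear model returns 1.00. The common-baseline linear model returns 2 × (2+ρ)/(5+ρ) = 2 × 2.5/5.5 = 0.91, an attenuation of 9%. With visits as categories, the year-end contrast is not attenuated, and its gain is the two-wave figure.

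**The case against.** The strongest reply is that nothing here is misstated. The free-baseline mixed model is valid, its effect is a change, the primary outcome is a change, and the sample size appears to rest on the same kind of contrast. A condensed article may also list effects of interest without giving the full parameterisation. All of this stands as to validity. The terms are nevertheless stated, and read literally they include a treatment main effect at baseline, so the point concerns what is written and not an omission.

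Second, a common baseline is not free of risk. It requires that the pupils measured at baseline be comparable across arms. The article describes school randomisation and parental consent but not their order. If consent or baseline measurement followed allocation and differed by arm, the constraint could introduce bias that the free-baseline model avoids. Linear time adds the attenuation shown in step 5, and the Discussion's statement that the primary interventions began in July makes a late effect conceivable. Both points stand and shape the fix.

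Three stronger readings are tempting and are not supported:
- **The planned result is biased by chance baseline imbalance.** The change contrast is unbiased over randomisation. Regression to the mean given an observed imbalance is the same efficiency point in other words.
- **The absence of age and sex contributes to the loss.** The article does not exclude covariates, and a covariate list is commonly left to the analysis plan. Main effects of fixed pupil characteristics also leave treatment-by-time unchanged in complete, balanced data: in a check with 200 pupils, the variance was 0.0050 with and without them.
- **Baseline adjustment makes 640 pupils worth about 850.** That is 640/0.75 = 853, which ignores schools, whereas 640 is explicitly the figure before clustering.

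**Conclusion.** The point holds as a missed efficiency of minor weight. The model as listed estimates an unadjusted change contrast for BMI, and likewise for body fat percentage. Using the baseline value would lower the variance by about 25% before clustering at the plan's correlation of 0.5. With clustering, the reduction is about 6% to 23% for the three-wave slope (5.5% to 21% for a year-end contrast).

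The clustered range rests on assumed values for school size, ICC and persistence of school effects, because the article gives none of them. Gains are smaller the more school effects persist and the higher the true pupil-level correlation. The coding of four arms as nudge or control is a separate matter and plays no part in this result.

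**What to change.** In section 2.6, or in the analysis plan before outcome data are examined by arm:

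- Analyse mid-year and year-end BMI, and body fat percentage, in the same linear mixed model with the school effect. Either adjust for the baseline value or keep baseline in the response with one common mean across arms.
- Enter follow-up visits as categories, or name the year-end contrast as primary, so that an effect that does not grow linearly is not attenuated.
- Keep the free-baseline model as a sensitivity analysis.
- Confirm and report that consent and baseline measurement did not depend on allocation. If they did, keep the free-baseline model as primary.

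The cost is a few lines of analysis wording. No extra data, visits or software are needed, and the planned sample size is unaffected. Adjusting for baseline as a covariate drops pupils without a baseline value unless these are handled separately; the common-baseline form retains them. The real price is the comparability assumption, which the confirmation above addresses.
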